## Abstract

**Rationale and aims:**

Monotherapy with antiplatelet agents is only modestly effective in secondary prevention of ischemic stroke (IS), particularly in patients with multiple risk factors such as cervicocephalic arterial stenosis, diabetes, and hypertension. While dual antiplatelet therapy (DAPT) with aspirin and clopidogrel reduced IS recurrence, particularly in the early stages after IS, it increased the risk of bleeding. Compared with aspirin, cilostazol prevented IS recurrence without increasing the incidence of serious bleeds. In patients with intracranial arterial stenosis, no significant increase in bleeding events was observed for DAPT with cilostazol and aspirin, compared to that for aspirin monotherapy. DAPT involving cilostazol may therefore be safer than conventional DAPT. These findings prompted us to conduct the Cilostazol Stroke Prevention Study for Antiplatelet Combination (CSPS.com; ClinicalTrials.gov identifier: NCT01995370) to evaluate the safety and efficacy of DAPT involving cilostazol for secondary IS prevention, in comparison with that of antiplatelet monotherapy.

**Design:**

The CSPS.com is a multicenter, randomized, open-label, parallel-group trial. A total of 4000 high-risk patients with noncardioembolic IS will be randomized 8–180 days after onset to receive aspirin or clopidogrel monotherapy, or DAPT with cilostazol and aspirin or clopidogrel for at least one-year.

**Study outcomes:**

The primary outcome is IS recurrence. Secondary outcomes are composite occurrences of any stroke, death from any cause, myocardial infarction, vascular death, and other vascular events.

**Discussion:**

The CSPS.com is expected to provide evidence indicating whether secondary IS prevention in high-risk patients can be improved by using DAPT involving cilostazol.

## Introduction and rationale

Antiplatelet therapy is a standard strategy for prevention of recurrent noncardioembolic stroke, in addition to lifestyle modifications and risk factor management. A previous meta-analysis found that conventional antiplatelet agents reduced the relative risk for stroke by about 20% in patients with a history of ischemic stroke (IS) or transient ischemic attack (TIA) 1. However, more effective antiplatelet therapy is needed in patients with intracranial arterial stenosis, carotid stenosis, or multiple vascular risk factors, because these conditions are associated with a higher risk of recurrence 2–6.

Since antiplatelet agents act through a range of mechanisms, the combination of dual agents can produce more effective stroke prevention. For example, the combination of aspirin with extended-release dipyridamole showed a superior effect on the prevention of recurrent IS, compared with aspirin alone 7,8. However, the efficacy of this combination could not be verified in a double-blind trial in Japan 9, and dipyridamole remains unapproved in Japan for prophylaxis of IS recurrence. Although relatively short-term combinations of aspirin and clopidogrel seem to prevent IS recurrence in patients with IS/TIA more effectively than aspirin alone 10–13, long-term usage is not generally recommended because it increased the incidence of serious hemorrhage and produced little reduction in the incidence of vascular events 14–16.

In the initial Cilostazol Stroke Prevention Study (CSPS) 17, this phosphodiesterase 3 inhibitor was shown to decrease IS recurrence without increasing serious bleeding, as compared with placebo. Cilostazol also decreased stroke [IS, intracerebral hemorrhage (ICH), or subarachnoid hemorrhage (SAH)] and halved serious bleeding as compared with aspirin in the second CSPS (CSPS 2) 18. In addition, a combination of cilostazol with aspirin for IS patients with intracranial arterial stenosis was investigated in three small studies 19–21; the Trial Of Cilostazol in Symptomatic intracranial arterial Stenosis (TOSS) 19 showed reduced stenosis progression, and all three studies found relatively few bleeding events, as compared with aspirin alone or aspirin plus clopidogrel.

In patients with peripheral arterial disease, the addition of cilostazol to a therapy with aspirin and/or clopidogrel did not increase bleeding times, compared with either agent alone 22. In another study of patients with peripheral arterial disease, the incidence of hemorrhagic events was comparable in subjects receiving cilostazol and in those receiving placebo 23. In a meta-analysis of randomized controlled trials in patients with a drug-eluting stent, the incidence of hemorrhagic events in the group receiving triple antiplatelet therapy (cilostazol plus aspirin and clopidogrel) was similar to that in the group receiving dual antiplatelet therapy (DAPT) with aspirin and clopidogrel 24. Thus, the addition of cilostazol may enhance the preventive effects of classical antiplatelet agents (aspirin, clopidogrel) in high-risk IS patients, without increasing hemorrhagic risk.

Animal studies have suggested that cilostazol protected mice from cerebral bleeds by reducing matrix metalloproteinase (MMP)-9 activity, and by preventing blood-brain barrier opening by inhibiting loss of claudin-5 expression 25–27. Cilostazol also increased intracellular cAMP concentration, thereby promoting the barrier function of tight junctions in brain capillary endothelial cells. Since the cAMP-dependent induction of claudin-5 expression is implicated in the promotion of endothelial cell tight junctions, the protection of endothelial cells may be explained by the phosphodiesterase-III inhibitory activity of cilostazol.

The Cilostazol Stroke Prevention Study for Antiplatelet Combination (CSPS.com; (ClinicalTrials.gov identifier: NCT01995370) will investigate the preventive effect of DAPT including cilostazol on IS recurrence in high-risk patients with noncardioembolic IS. Patients receiving cilostazol together with aspirin or clopidogrel will be compared with those treated with aspirin or clopidogrel monotherapy.

## Methods

### Design

The CSPS.com is a multicenter, randomized, open-label parallel-group trial. All trial centers are required to receive approval from the relevant ethics committee before initiation of the trial. Written informed consent must be obtained from each patient before enrollment. This trial is registered with ClinicalTrials.gov (NCT01995370) and the UMIN Clinical Trials Registry (000012180). Figure 1 shows a flowchart of the trial design. Table 1 shows the schedule of observations, examinations, and assessments.

**Figure 1 fig01:**
[figure not shown]
Trial design flowchart. Change in the dose of aspirin or clopidogrel will not be permitted after informed consent is obtained. Cilostazol treatment can be started with 100 mg/day, provided the dose is increased to 200 mg/day within 15 days.

**Table 1 tbl1:** Trial schedule

Assessment	Period								
	(Date of onset)	Registration	Start date of observation	1 M	3 M	6 M	12 M	Thereafter, every 6 months	Completion of observation (*)
Informed consent		○							
Demographics		○							
Modified Rankin Scale (mRS)			○	○	○	○	○	○	○
Compliance status of trial drugs			○	○	○	○	○	○	○
Concomitant medication			○	○	○	○	○	○	○
Blood pressure			○	○	○	○	○	○	○
Head MRI		○							
Head MRA, T2*WI		△							
Carotid artery imaging (US, CTA, MRA)		△							
Laboratory test (blood)		○							
Laboratory test (urine)		○							
Chest X-ray		○							
ECG		○							
Adverse event									

* When patients are withdrawn from the trial, or one-year after the start of the protocol treatment in the last patient.

○, required; △, optional.

### Patient population

Patients who have developed noncardioembolic IS between 8 and 180 days before the start of the protocol treatment are the target population of the trial. Inclusion and exclusion criteria are listed in Table 2. Patients are asked to continue taking clopidogrel or aspirin alone as an antiplatelet and could not change the agent once providing informed consent. Stenosis (≥50%) of a major intracranial or extracranial artery, or two or more of the vascular risk factors listed in Table 2, is essential as an indicator of a high risk of IS recurrence.

**Table 2 tbl2:** Inclusion and exclusion criteria

Inclusion criteria: 1) Clinical diagnosis of noncardioembolic IS that developed between 8 and 180 days before the start of the protocol treatment 2) A responsible lesion identified on MRI 3) Age 20–85 years 4) Taking clopidogrel or aspirin alone as antiplatelet therapy when providing informed consent 5) At least one of the following (a–c): a. ≥50% stenosis of a major intracranial artery (to the level of A2, M2, or P2) b. ≥50% stenosis of an extracranial artery (the common carotid artery, internal carotid artery, vertebral artery, brachiocephalic artery, or subclavian artery) c. Two or more of the following risk factors – Age ≥ 65 years – Diabetes mellitus – Hypertension – Peripheral arterial disease – Chronic kidney disease – History of IS (excluding the index IS for this trial) – History of ischemic heart disease – Smoking (only current smokers) 6) Considered to be able to visit the trial site for ambulatory care throughout the observation period 7) Written informed consent by the patient
Exclusion criteria: 1) High-risk sources of cardioembolism, according to the TOAST classification 2) Using any anticoagulants 3) Contraindication to MRI examination, such as claustrophobia or implanted pacemaker 4) Scheduled to undergo any surgery, such as percutaneous angioplasty, stent placement, and bypass grafting, during the trial period 5) Drug-eluting coronary stent implanted within one-year 6) History of symptomatic nontraumatic intracranial hemorrhage, any other hemorrhagic disease, bleeding predisposition, or blood clotting disorders 7) History of hypersensitivity to cilostazol 8) Congestive heart failure or uncontrolled angina pectoris 9) Thrombocytopenia (platelet count, ≤ 100,000/mm^3^) 10) Severe liver or renal dysfunction 11) Pregnant, breast-feeding, or of child-bearing potential 12) Malignant tumor requiring treatment 13) Aspirin user meeting any of the following criteria: History of hypersensitivity to aspirin or salicylic acid analogues Current peptic ulcer Aspirin-induced asthma or its history 14) Clopidogrel user with a history of hypersensitivity to clopidogrel 15) Participating in any other clinical studies 16) Unsuitable for trial enrollment, as judged by the investigator

TOAST, the Trial of Org 10172 in Acute Stroke Treatment.

### Randomization

The data center will randomize the patients to either monotherapy group or DAPT groups using a block-randomization scheme, with the research site as a randomization unit. After providing informed consent, each patient will be identified by a linkable patient identification code, and registered via a web-based registration system, along with information relevant to his or her eligibility. If the patient is considered eligible, the allocated therapy for the patient will be notified through this system. Patients and investigators will be aware of the treatment allocation.

### Treatments

Patients in the monotherapy group will receive oral aspirin (81 or 100 mg) or clopidogrel (50 or 75 mg), once daily. Clopidogrel at 50 mg is approved for older (for example ≥75 years old) or low-weight patients (≤50 kg body weight) in Japan. Patients in the DAPT group will receive oral cilostazol (100 mg, twice daily; the recommended dose in Japan) and either aspirin (81 or 100 mg) or clopidogrel (50 or 75 mg), once daily. To prevent adverse drug reactions such as headache and tachycardia, cilostazol treatment can be started at 100 mg/day, and increased to 200 mg/day within 15 days. If the patient experiences minor cilostazol-related adverse reactions including headache, palpitation, nausea, and vertigo, the trial can be continued using the reduced cilostazol dose of 100 mg/day. Change in the choice of these three antiplatelet medications will not be permitted after informed consent is obtained. Temporary suspension of the trial treatment is permitted during invasive treatment such as surgery, but cannot exceed four-weeks. Use of any concomitant treatment with any antiplatelet or anticoagulant agent (other than trial drugs) will be prohibited.

Patients will be withdrawn from the trial when they experience any cardiovascular events corresponding to the primary and secondary outcomes, or when the trial treatment has been suspended for more than four consecutive weeks.

### Primary outcome

The primary outcome is a recurrence of IS, with the symptoms lasting for at least 24 h.

### Secondary outcomes

Any stroke (IS, ICH, and SAH)

SAH or ICH

IS or TIA

Death from any cause

Stroke, myocardial infarction (MI), or vascular death

All vascular events, including stroke, MI, and other vascular events (e.g., aortic dissection; aortic rupture; pulmonary embolism; heart failure, angina pectoris or peripheral artery disease requiring hospitalization; revascularization of coronary artery, aorta, cephalocervical artery, and peripheral arteries).

Safety outcomes are adverse events, adverse drug reactions, and severe or life-threatening hemorrhage as defined in the Global Utilization of Streptokinase and Tissue Plasminogen Activator for Occluded Coronary Arteries (GUSTO) classification, which includes ICH and hemorrhage resulting in substantial hemodynamic compromise requiring treatment 28.

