### Study organization and funding

Otsuka Pharmaceutical Co., Ltd. sponsored the trial implementation in the Japan Cardiovascular Research Foundation under an agreement between the two parties. Subject registration, data management, and statistical analysis are delegated to a contract research organization (EPS Corporation). This trial will be conducted at approximately 400 sites under the guidance of the steering committee. The enrolled patients have to pay partly their own costs for drugs prescribed in this study depending on the type of their own health insurance.

The principal investigator is [name], who is attached to the National Cerebral and Cardiovascular Center. The final trial protocol was prepared by the protocol committee, and it will be amended, if required. Any event related to the primary and secondary end-points will be reviewed by the event review committee blindly to antiplatelet medications. The statistical analysis committee will be responsible for proposing the randomization scheme and providing expert opinions on the sample size and the analysis plan. It will be also responsible for generating the interim and final analysis plans.

The IDMC will recommend trial discontinuation/continuation or protocol amendment based on annual reviews of patient accrual, serious adverse events, incidence of adverse events, and on the interim efficacy analysis comparing the two treatment arms. The individuals who played a critical role in the planning, supervision, and conduct of this trial are listed in the end of this article.

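### Revascularization with no stated limit on indication counts as a secondary outcome event and, through the withdrawal rule, also ends observation for the primary outcome

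*Protocol article*

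**What the plan says.** All references are to the protocol article.

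- **Secondary outcomes.** The last of six outcomes, all vascular events, includes "revascularization of coronary artery, aorta, cephalocervical artery, and peripheral arteries". Heart failure, angina and peripheral artery disease count in the same list only if they lead to hospital admission. Revascularization has no comparable qualifier.
- **Patient population, Table 2.** Criteria 5a and 5b admit patients with "≥50% stenosis of a major intracranial artery" or "≥50% stenosis of an extracranial artery". Exclusion 4 removes patients "Scheduled to undergo any surgery, such as percutaneous angioplasty, stent placement, and bypass grafting, during the trial period".
- **Randomization.** "Patients and investigators will be aware of the treatment allocation".
- **Treatments.** "Temporary suspension of the trial treatment is permitted during invasive treatment such as surgery, but cannot exceed four-weeks". The next paragraph states: "Patients will be withdrawn from the trial when they experience any cardiovascular events corresponding to the primary and secondary outcomes".
- **Table 1, footnote.** Observation is complete at withdrawal, or one year after the last patient starts protocol treatment.
- **Statistical analysis.** Efficacy and safety are analysed in the intention-to-treat population.
- **Study organization and funding.** "Any event related to the primary and secondary end-points will be reviewed by the event review committee blindly to antiplatelet medications".

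**The concern.** A patient can enter with a stenosis that nobody plans to treat, and a clinician who knows the arm can later decide to treat it without new symptoms. As written, that procedure has two consequences.

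First, it is an efficacy event in the all-vascular-events composite. A difference between arms in that composite could then partly reflect willingness to intervene rather than disease.

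Second, and more important, it is a withdrawal event, and withdrawal ends observation. The patient's later time at risk for ischemic stroke is lost to the primary analysis, including any stroke around the procedure. Patients chosen for revascularization are unlikely to have the same stroke risk as those who are not, so this censoring may be informative. If knowledge of the arm influences the choice, it may also differ between groups. An intention-to-treat analysis normally follows every randomized patient for the primary outcome whatever happens to treatment.

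Third, the suspension sentence and the withdrawal sentence can both apply to the same procedure. The article does not state how they relate.

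**Working it through.** **Reading the rules together**

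1. Revascularization is a component of a secondary outcome (Secondary outcomes).
2. A cardiovascular event matching a secondary outcome leads to withdrawal (Treatments).
3. Withdrawal completes observation (Table 1 footnote).
4. Hence revascularization ends observation for ischemic stroke, although it is not part of the primary outcome.
5. Exclusion 4 uses the word surgery to cover angioplasty, stenting and bypass. The suspension sentence refers to invasive treatment such as surgery. A later stent or bypass can therefore fall under both the suspension sentence and step 2.

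**Inputs for the size of the information loss** (Sample size section): 4% annual recurrence on monotherapy; 30% relative reduction; two-sided 0.05; 80% power; 2.5 years of recruitment; 3.5 years maximum follow-up; 5% annual discontinuation; 2000 per group. The article gives no revascularization rate, so 1% and 3% per year are assumptions.

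**Formula.** With exponential times, uniform accrual and follow-up of 1 to 3.5 years, the probability of an observed event is

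π(λ, δ) = (λ/h) × [1 − (e^(−h) − e^(−3.5h)) / (2.5h)], with h = λ + δ,

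where λ is the stroke hazard and δ the hazard of leaving observation.

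**Step 1: the plan's own figure.** Required events = 4 × (1.960 + 0.842)² / (ln 0.7)² = 247. With λ = 0.04 and 0.028 and δ = 0, π = 0.0857 and 0.0609, mean 0.0733. Then n = 247 / (2 × 0.07328) ≈ 1686 per group, against 1688 stated. The model matches the plan.

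**Step 2: expected primary events at 2000 per group.** Take λ = −ln 0.96 = 0.0408, 0.7 × 0.0408 = 0.0286, and δ = −ln 0.95 = 0.0513.

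- π = 0.0822 and 0.0584
- Events: 164.3 + 116.7 = 281
- Person-years: 164.3/0.04082 + 116.7/0.02858 ≈ 8,109

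**Step 3: add withdrawal for revascularization at rate r to δ.** Power = Φ(½ × √events × |ln 0.7| − 1.96).

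| Assumed r per year | Expected primary events | Power |
|---|---|---|
| 0 | 281 | 0.848 |
| 1% | 162.4 + 115.3 ≈ 278 | 0.844 |
| 3% | 158.6 + 112.6 ≈ 271 | 0.836 |

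Using 4% directly as the hazard gives 276, 272 and 266 events, and power 0.842, 0.837 and 0.829. The conclusion is the same.

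Step 3 treats leaving as unrelated to stroke risk. It measures lost information, not bias. The documents give no basis for sizing the bias or giving its direction.

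**Step 4: illustration for the composite.** Suppose other vascular events run at an assumed 5% per year with hazard ratio 0.70, and procedures unaffected by treatment are added at r% per year. The composite ratio is about (0.7 × 5 + r)/(5 + r): 4.0/5.5 = 0.73 at r = 0.5, 4.5/6 = 0.75 at r = 1, and 5.5/7 = 0.79 at r = 2. So the composite is diluted even if the arm has no influence on the decision to intervene.

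**The case against.** Several counter-arguments have force.

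- **The two Treatments sentences can be read together.** Suspension is a permission concerning study drug, while withdrawal is mandatory. A site could suspend for procedures that are not outcome events and withdraw for those that are. This stands. A reader might infer that the sentences are incompatible and that sites will handle these patients differently, but the text does not establish either. What remains is that the article does not state the relation, and its own use of the word surgery makes the overlap real.
- **Elective procedures are not mentioned.** True. The point is only that nothing in the definition leaves them out.
- **An article condenses the full protocol.** Detailed event definitions may sit elsewhere, and the list is given as examples. This weakens the point about the missing qualifier. It does not weaken the point about observation, because the withdrawal rule and the end-of-observation rule are both stated.
- **Event review is blinded.** Blinded review can confirm that a procedure took place. It cannot undo the influence of known allocation on the decision to perform it.
- **Exposure is limited.** Revascularization enters one of six secondary outcomes and not the primary. The composite of stroke, myocardial infarction or vascular death leaves it out. This stands, and it bounds the outcome-definition part.
- **A symptom criterion is itself open to bias.** Symptoms are reported by unblinded patients to unblinded clinicians, and hospital admission for angina or heart failure is open to the same influence. This also stands, so that part of the fix is only a partial remedy.

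**Conclusion.** The point holds in this form: a procedure chosen by unblinded clinicians, possibly for a stenosis present at entry, is counted without limit in one secondary composite and, under the stated rules, ends observation for ischemic stroke. The second consequence is at odds with the intention-to-treat analysis and may be informative censoring.

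The cost in power is small: about 281 expected primary events fall to about 278 to 271, with power down by about 0.01 at most, if an assumed 1 to 3% per year leave in this way. The reason to act is bias in follow-up and the reading of one of six secondary outcomes.

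A reader might go further and put a number on the bias by multiplying an assumed procedure rate by an assumed difference between arms in the decision to intervene. The documents give neither figure. An overall procedure rate would also include urgent, symptom-driven procedures, which are not in question. No such number or direction is claimed here.

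**What to change.** 1. **Observation.** State that revascularization does not by itself end observation for the primary outcome, and follow these patients to trial end whatever their treatment. This is the main change.
2. **Outcome definition.** Have the blinded event review committee classify each revascularization as prompted by new or worsened ischemic symptoms or not. Count only the former in all vascular events, or report that version alongside the current one, and report the other procedures separately. Record the indication, and whether the lesion was documented at registration, on the event form.
3. **Treatments section.** Reconcile the suspension and withdrawal sentences so that it is clear how each applies when the invasive procedure is itself an outcome event. The treatment rule is for the sponsor to decide.

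The cost is some further follow-up visits, an added field on the event form, short text changes, and slightly fewer events in one secondary composite. The symptom criterion reduces open-label bias only in part.
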